# Protocol for a pilot trial to assess the feasibility of the Move More @ Work intervention to encourage employees to take the opportunity to move (be physically active) after every 30 min of sitting

**DOI:** 10.1186/s40814-021-00903-2

**Published:** 2021-09-07

**Keywords:** Sedentary behaviour, Prolonged occupational sitting, Regular activity breaks, Behaviour change, Workplace health promotion, Accelerometry, Interrupted time series design

## Abstract

**Background:**

Prolonged sitting increases the risk of cardio-metabolic disease. Office-based employees are particularly susceptible to high rates of this sedentary behaviour during work hours. Laboratory studies indicate that regularly interrupting periods of prolonged sitting with short bouts (2 min) of physical activity can improve markers of cardio-metabolic health. This method of interrupting sitting time is yet to be tested in an occupational setting and may provide an alternative to providing sit-to-stand desks. Drawing on the Behaviour Change Wheel and evidence on the barriers and motivators to performing regular activity breaks, the Move More @ Work intervention was developed. The objectives of this pilot study are to examine the feasibility, and preliminary outcomes, of this intervention designed to encourage participants to perform 1–2 min of activity after every 30 min of continuous sitting throughout the work day. The study will inform if progress to a full effectiveness trial is warranted.

**Methods:**

An interrupted time series design consisting of a 4-week baseline (control period), a 12-week intervention, and a 12-week follow-up will be utilised. At least 57 university employees who self-report spending > 5 h per day sitting at work on at least 3 days per week will be recruited to participate. The intervention consists of (1) a structured consultation with a Move More @ Work coach, containing a number of behaviour change techniques to create an individualised plan of how to incorporate the activity breaks into the working day, and (2) strategies to create a supportive workplace culture for performing the activity breaks. Feasibility will be assessed by recruitment and retention rates, and acceptability of the intervention. Pilot outcomes are the number of regular activity breaks taken during the workday, cardio-metabolic risk score and self-reported health, and work-related productivity outcomes.

**Discussion:**

If the Move More @ Work intervention is shown to be feasible, acceptable, and shows evidence of effectiveness, this will provide justification for the progression to a full scale evaluation of the intervention. In the longer-term, this intervention may provide an alternative means of improving health outcomes through interrupting sedentary time than that offered by current sedentary behaviour interventions.

**Trial registration:**

Australian New Zealand Clinical Trials Registry, ACTRN12620000354987. Registered on 12 March 2020

**Supplementary Information:**

The online version contains supplementary material available at 10.1186/s40814-021-00903-2.

## Background

Sedentary behaviour — seated or reclined activities involving low energy expenditure [1] — predominate the waking hours of most adults. Total sedentary behaviour is accumulated across the day as a consequence of a number of life events, e.g., watching TV, car travel, and work-related tasks. Sustained bouts of sitting have been associated with increased incidence of diabetes, cardiovascular disease, some cancers, and overall mortality [2–4]. Those in office-based employment are particularly susceptible to high rates of this sedentary behaviour during work hours [5]. Observational studies have shown that the pattern in which total sedentary time is accumulated also influences these negative outcomes. Individuals who accumulate their sedentary time in long uninterrupted bouts (periods > 60 min) have a poorer cardio-metabolic risk factor profile (higher waist circumference, body mass index [BMI], fasting glucose and triglyceride concentrations) than those whose total sedentary time is the same but is accumulated in short bouts interspersed with light or moderate intensity activity [6, 7]. These associations appear to be consistent across age, sex, and ethnic subgroups [6], and occur even in those who engage in large amounts of leisure time moderate-to-vigorous physical activity [6, 7]. Additionally, at least in older women, those who have the longest bouts of uninterrupted sedentary time are 22% (95% CI, 1 to 46%) more likely to develop cardiovascular disease compared to those with shorter bouts [8]. Tightly controlled laboratory or office-based studies have shown that regularly interrupting periods of prolonged sitting (every 20–30 min) with a short bout of activity (2 min) results in improvements to postprandial glucose and lipid metabolism in healthy adults [9, 10] and those with obesity and type 2 diabetes [11]. Importantly, when prolonged sitting is interrupted with only short bouts of standing, the results on postprandial metabolism are smaller in magnitude and less consistent [9, 10].

The majority of field-based intervention studies that aim to reduce occupational sitting have provided individuals with standing, or sit-to-stand workstations. A systematic review and meta-analysis of the use of activity-permissive workstations [12] reported decreases in sedentary behaviour of up to 1.6 h over an 8 h work day, and some modest improvements in markers of cardio-metabolic health. An intervention where participants take the opportunity to perform short (1–2 min) bouts of activity (e.g., walking, simple body weight resistance exercises) to interrupt periods of prolonged sitting daily over a period of weeks and months has the potential to successfully attenuate the risks associated with prolonged sitting. This novel intervention addresses the call for much needed, well-designed, evidence-based research to reduce sitting time [13] and has the potential to dramatically extend knowledge in the field of sedentary behaviour by providing an alternative to the provision of standing desks as a means to interrupt sedentary time. Yet to substantiate these claims, the intervention must first be subject to a feasibility study to test the research methods, implementation, and acceptability to participants and provide an indication of effectiveness [14]. The feasibility study will effectively answer the question, ‘will the intervention increase the number of short bouts of activity people perform at work?’ Previous research has typically used the term ‘regular activity break’ to describe these short bouts of activity taken at regular intervals during the day. From here on, and throughout our intervention, we will refer to these breaks as ‘opportunities to move’, rather than activity breaks. Through our preliminary research on workplace culture conducted in preparation for the intervention, senior management expressed concern that the term ‘activity break’ may be misconstrued by employees as a contracted break offered as part of an employment contract. Consequently, we want to avoid using the term ‘break’.

The feasibility of making sustained behaviour changes from prolonged sitting to taking regular opportunities to move in an occupational setting has not been studied. Like most behaviour change interventions, a key factor is understanding if individuals will adhere to the intervention and how best to motivate them to perform this activity. A recent systematic review of behaviour change strategies used in interventions designed to reduce general sitting time concluded that interventions performed to date have given insufficient attention to motivation [13]. This review found self-regulatory skills (self-monitoring of behaviour, action and coping planning, feedback), education, and environmental restructuring were important strategies to support behaviour change [13]. To specifically explore factors that would support and hinder the ability to take an opportunity to move and provide essential knowledge for the development of this Move More @ Work intervention, we conducted focus group research with office-based employees [15]. Our work found that behavioural prompts, rewards, the ease of incorporating opportunities to move into the work day and having external support were important strategies to facilitate behaviour change. In conjunction, we found a number of social and individual barriers that need to be overcome including, perception of lowered work productivity, workplace social norms and culture, and type of work task [15]. These have also been shown to be barriers to reducing sitting time [16, 17]. To increase the individual’s perceived ability to take an opportunity to move and reduce their sedentary behaviour, interventions need to employ these behaviour change techniques and employ strategies to overcome the unique barriers people face [13].

In designing the Move More @ Work intervention, we drew on the Behaviour Change Wheel [18] and its associated COM-B model (Capability, Opportunity, Motivation and Behaviour [18];) and theoretical domains framework (TDF [19];) to provide an integrated synthesis of the key behaviour change constructs and specific behaviour change techniques that would provide the mechanisms of action for individuals to incorporate more movement into their work day. This comprehensive framework is instrumental to inform intervention design and evaluation [18] and has been used in other sedentary behaviour interventions [17]. The COM-B model identifies that to encourage people to take opportunities to move requires improved capability, opportunity, and motivation. The TDF represents key concepts from behaviour change theory that can be used to structure the important components required when implementing an intervention (e.g., knowledge, goals, environmental context, and resources).

## Objective

The objective of this pilot study is to assess the feasibility, and potential effectiveness, of the Move More @ Work intervention designed to encourage staff to take 1–2-min opportunities to move after every 30 min of prolonged sitting over the work day. An opportunity to move is defined as greater than 1 min of light to moderate activity involving repeated movement of some kind (e.g., brisk walking, body weight resistance exercises, or moving through a series of stretches). The study will inform if progress to a full effectiveness trial is warranted. The specific aims of this study are the following:
Evaluate the recruitment rate of participants into the study, and retention of those participants through the intervention and post-intervention period.Qualitatively examine the acceptability of the Move More @ Work intervention to participants, workplace management, and where possible, employees not involved in the intervention but working in close proximity to those that were.Evaluate the extent to which Move More @ Work changes the number of opportunities to move taken over the work day and the extent of participant adherence to the intervention.Examine the potential effects of Move More @ Work on Cardio-Metabolic Risk score (an estimated risk based on waist circumference, blood pressure, fasting glucose, triglycerides and High Density Lipoprotein [HDL] cholesterol), musculoskeletal health, psychological well-being, and perceptions of work productivity.Use the findings to refine the intervention and inform the development of a subsequent effectiveness trial of the Move More @ Work intervention.Estimate the sample size required in a subsequent effectiveness trial evaluating the intervention.

## Methods

### Study design and setting

An interrupted time series design will be utilised in this study [20, 21]. With this design, there will be no control group but instead there will be two pre-intervention assessments, a post-intervention assessment and a follow-up assessment 12 weeks post-intervention. This quasi-experimental design can be used instead of a randomised controlled design to estimate an intervention effect in situations where randomisation is not feasible. In this case, the interrupted time series design is used to avoid the high risk of contamination between a control group and an intervention group, where these groups could be in close working proximity. The study will be conducted at the University of Otago, Dunedin, New Zealand. In this large workplace open-plan offices are commonplace, movement between offices is common, and it is possible that while taking opportunities to move, intervention group participants could mix with control group participants. Data will be collected between August 2020 and February 2021.

There will be four time points for data collection (not all variables will be collected at all time points — see “Outcomes” section below for details): Baseline (T1) and 3 weeks later at time 2 (T2) which corresponds to the pre-intervention period, at completion of the 12 week intervention (T3), and then after the 12 week post-intervention follow-up period (T4). Figure 1 shows the study flow diagram. This study has been approved by the University of Otago Human Ethics Committee (ref H20/028). This protocol has been prepared in accordance with the Standard Protocol Items: Recommendations for Interventional trials (SPIRIT) 2013 statement [22], the SPIRIT schedule of enrolment, interventions, and assessments is presented in Table 1. The SPIRIT Checklist can be found in Additional File 1. This study is registered with the Australian New Zealand Clinical Trials Registry: ACTRN12620000354987 (Additional File 2). Protocol version 2 dated June 2020.

**Fig. 1 Fig1:**
[figure not shown]
Flow diagram of the Move More @ Work feasibility and pilot trial

**Table 1 Tab1:**
[figure not shown]
The schedule of enrolment, interventions, and assessments for the Move More @ Work study using an interrupted time series design

### Outcomes

#### Feasibility

Drawing from recommendations [23], feasibility will be assessed through recruitment and retention rates assessed at pre-intervention through to T4. Acceptability will be assessed through participant feedback on satisfaction with the conduct of the intervention, and usefulness of the specific intervention components collected at T3.

#### Pilot study primary outcome

The primary outcome is workday physical activity behaviour, specifically, the change in the mean number of opportunities to move taken during a workday from the pre-intervention period (T1 and T2) to the end of the intervention (T3) and post-intervention (T4) periods. An estimated change will be calculated, along with an estimate of the within-person variability, which can then be used in sample size calculations for future studies.

#### Pilot study secondary outcomes

Secondary outcomes are health- and work-related outcomes. Specifically, cardio-metabolic risk score will be measured at pre-intervention T2 and assessed by changes from T2 to the end of the intervention (T3) and post-intervention (T4) periods. Results of any change in health outcomes between T2 and T3 will be used to inform the sample size for a future effectiveness trial which will likely have health variables as the primary outcome.

Finally, musculoskeletal health, psychological well-being, occupational fatigue, the impact of health on work, and physical activity patterns outside of work will be assessed by changes from the pre-intervention period (T1 and 2) to the end of the intervention (T3) and post-intervention (T4) periods.

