### Pilot study outcomes

All measures (except blood-related measures) will be taken pre-intervention T1 and T2, end of the 12-week intervention (T3), and after a 12 week follow-up period (T4).

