#### Cardio-metabolic risk score

Cardio-metabolic risk assessment will be undertaken at pre-intervention T2. This assessment comprises measures of waist circumference, weight, height, blood pressure, triglycerides, HDL, and fasting glucose. Waist circumference will be measured to the nearest 0.1 cm with a steel measuring tape at the midpoint between the lowest rib and the iliac crest. Weight will be measured to the nearest 0.1 kg with the participant wearing light clothing and no shoes using calibrated body weight scales. Height will be measured to the nearest 0.1 cm, without shoes, with the individual looking straight ahead (Frankfort plane), using a calibrated stadiometer. All anthropometric measurements will be taken in duplicate, with a third measurement taken if the first two differ by more than 0.5 units. Blood pressure will be measured via a digital blood pressure monitor (OMRON HEM-907; Omron Healthcare, Japan) using the right arm and appropriately sized cuff. Participants will rest in a seated position for 15 min prior to having three measurements taken at 1-min intervals. Fasting blood samples will be collected at the Department of Human Nutrition Research Clinic in the morning by a trained phlebotomist for the analysis of glucose and lipids (triglycerides, HDL cholesterol). Samples will be centrifuged within an hour of collection and plasma stored at – 80 °C until analysis, which will be conducted in the Department of Human Nutrition Diabetes and Lipids Laboratory. Lipid and glucose concentrations will be measured using glycerol phosphate oxidase and hexokinase enzymatic methods, respectively, on a Cobas C 311 analyser.

The overall cardio-metabolic risk score will then be calculated by first log10 transforming and normalising (mean/SD) the relevant biomarkers and then taking a weighted average of their values: 1/5 waist circumference + 1/5 triglycerides − 1/5 HDL + 1/5 fasting glucose + 1/5 mean of systolic and diastolic blood pressure. This method has been used in previous research [32].

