### Data analysis

Descriptive statistics will be used to assess the feasibility outcomes of time taken to recruit and retention of participants across the intervention. Intervention acceptability will be assessed through analysis of participant interviews. They will be open-coded, examining for common themes in relation to acceptability and usefulness of the intervention. They will then be axially coded, investigating the relationships between the themes and the similarities and differences in individuals’ reporting and experiences of those themes [39].

The primary and secondary outcomes of the pilot study will be assessed using mixed effects regression models, where the independent variables in the model will be: time since baseline, pre-/post-intervention (dummy variable), and a time by pre-/post-intervention interaction variable. The immediate effect of the intervention will be represented by the regression coefficient of the pre-/post-intervention variable, with the regression coefficient of the interaction term representing the difference in change in the outcome over time. Because this study examines within-person changes, only participants with data at T1, T2, and T3 will be included in the primary analyses, using an intention-to-treat approach. Office clusters will be included as a random effect. Where appropriate, the Stata command ‘itsa’ (for interrupted time series analysis) will be used. Mean changes in outcomes with 95% CI will be reported. To illustrate the results of the pilot study and assist in interpretation, line graphs will be generated. No interim analysis is planned for the trial. All quantitative statistical analysis will be carried out using Stata (StataCorp, Texas).

To estimate sample sizes for a future effectiveness trial, standard deviations of the change in health outcomes (e.g., body weight, blood pressure, and lipids) between T2 and T3 will be calculated. Estimates of intraclass correlation coefficients (from office clusters) will also be used to estimate the design effect if the future trial is planned to be a cluster randomised controlled trial [40].

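### The pre/post-slope model assigned to all outcomes cannot be estimated for the cardio-metabolic risk score, which has only one pre-intervention measurement

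*Protocol article*

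**What the plan says.** **Schedule.** In the Protocol article, Pilot study secondary outcomes states "cardio-metabolic risk score will be measured at pre-intervention T2 and assessed by changes from T2 to the end of the intervention (T3" and adds T4 as the second comparison. The Cardio-metabolic risk score section repeats the timing: "Cardio-metabolic risk assessment will be undertaken at pre-intervention T2". Pilot study outcomes, under Measures, sets the general schedule and leaves blood out of it: "All measures (except blood-related measures) will be taken pre-intervention T1 and T2".

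**Composition.** The score is "1/5 waist circumference + 1/5 triglycerides − 1/5 HDL + 1/5 fasting glucose + 1/5 mean of systolic and diastolic blood pressure". Three of its five parts (triglycerides, HDL, fasting glucose) need a blood sample.

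**Model.** Data analysis says "The primary and secondary outcomes of the pilot study will be assessed using mixed effects regression models", with independent variables "time since baseline, pre-/post-intervention (dummy variable), and a time by pre-/post-intervention interaction variable". It reads the pre/post coefficient as the immediate effect and the interaction coefficient as the difference in change over time. No outcome is exempted. The section's qualifier about appropriateness attaches only to the use of the Stata interrupted time series command, not to the model.

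**Data rule.** The same section says "only participants with data at T1, T2, and T3 will be included in the primary analyses".

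**The concern.** A segmented model with separate levels and slopes needs at least two pre-intervention occasions, so that there is a prior slope to project forward. The opportunities-to-move outcome has two, T1 and T2. The risk score has one. The Pre-intervention period section presents the two early assessments as the control for study participation and time trends, but what it describes there is accelerometry. No such control exists for this score.

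Two sections therefore prescribe different analyses of one outcome: a change from T2 in the outcomes section, and a segmented regression in the analysis section. The second cannot be carried out as written. An analyst following it would have to remove a term after the fact, and the choice of term decides what the reported effect means. The score is the first-named secondary outcome and belongs to the study's aim on potential health effects.

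**Working it through.** The plan gives no figure for this outcome, so there is none to reproduce. The check is whether the stated model can be estimated on the stated schedule.

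**Inputs**
- T1 = week 0 and T2 = week 3 (Study design and setting).
- Four-week pre-intervention period (Pre-intervention period), then 12 weeks of intervention and 12 of follow-up: T3 ≈ week 4 + 12 = 16, T4 ≈ 16 + 12 = 28.
- Score available at T2, T3 and T4. Even if waist and blood pressure are taken at T1, three of the five components are missing there, so no T1 score can be formed.
- Fixed effects: intercept (a), time (b), pre/post (d), time × pre/post (c).

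**Rank.** The rows (intercept, time, post, time × post) are:
- T2: 1, 3, 0, 0
- T3: 1, 16, 1, 16
- T4: 1, 28, 1, 28

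Three rows support at most three parameters, and the rank is 3 against 4. Adding any multiple k of (a, b, d, c) = (−3, 1, 3, −1) leaves all three fitted means unchanged:
- T2: −3 + 3 = 0
- T3: −3 + 16 + 3 − 16 = 0
- T4: −3 + 28 + 3 − 28 = 0

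All four entries are non-zero, so none of the four coefficients is estimable. The rank is also 3 with T3 and T4 at weeks 15 and 27. With all four waves the rank is 4 and every coefficient is estimable, so the problem is specific to outcomes without a T1 value.

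**What remains if a term is dropped**
- Interaction dropped: b = (T4 − T3)/12, so d = T3 − T2 − 13b = T3 − T2 − (13/12)(T4 − T3). The follow-up slope stands in for the unmeasured prior trend.
- Time dropped: c = (T4 − T3)/12, so d = T3 − T2 − (16/12)(T4 − T3).
- Pre/post dropped: there is no level-change coefficient.

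Each surviving d equals T3 − T2 only if the T3 and T4 means are equal.

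**Does scatter in visit dates rescue it?** If time is each person's actual elapsed time, the matrix becomes full rank, but the prior slope then rests only on differences between people in when T2 happened to fall. Assumptions: n = 47 and within-person correlation 0.5 (both from Sample size, where they concern activity breaks), with normal scatter at each visit. Median standard errors of the week-4 step, in outcome SDs:

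| Scatter SD (weeks) | SE of step |
|---|---|
| 0 | not estimable |
| 0.15 | 0.86 |
| 0.30 | 0.47 |
| 0.50 | 0.35 |

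The simple T2-to-T3 change has SE √[2(1 − 0.5)/47] = √(1/47) = 0.15. Scatter therefore gives a nominal fit, not a usable one.

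**Data rule.** The number of participants with a score at T1 is 0. Applied to the outcome being analysed, the rule leaves 0 eligible. Applied to any T1 data, such as accelerometry, it leaves participants in.

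**The case against.** The strongest defence is that the outcomes section already defines the right quantity, change from T2 to T3 and T4, and Data analysis promises mean changes with 95% CIs. On that view only a linking sentence is missing, which an analysis plan could supply. It is true that the intended contrast is visible. But the article does not leave the model open: it names the outcomes covered, the terms and their interpretation, and that conflicts with its own schedule. This is a stated analysis that fails, not an omitted detail.

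Four stronger readings are tempting and not supported:

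- **That the data rule leaves nobody to analyse.** The rule speaks of participants with data and of the primary analyses. It can mean participant-level attendance or the primary outcome alone. Its rationale, within-person change, favours an outcome-by-outcome reading but does not settle it.
- **That the next trial's sample size is compromised.** Data analysis gives that task its own calculation, the SD of T2-to-T3 change in health outcomes, which does not use the segmented model. The progression criteria ask for estimates of variation, not for this score's pre/post coefficient.
- **That the effect would be doubled.** If a 0.20 improvement at T3 were wholly lost by T4, dropping the interaction gives 0.20 + (13/12)(0.20) = 0.417, and dropping time gives 0.20 + (16/12)(0.20) = 0.467. Both the benefit and its complete loss are invented inputs, and the document does not say which term would go. These figures illustrate the mechanism; they do not measure the plan's bias.
- **That standardisation forces the change to zero.** The scoring text says "first log10 transforming and normalising (mean/SD) the relevant biomarkers" without naming the reference sample. Standardising within each wave would give zero mean change for the same participants, but nothing says this will be done, and the method is attributed to earlier research not shown here.

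**Conclusion.** The concern holds for the model. For the cardio-metabolic risk score, the prescribed fixed effects have rank 3 for 4 parameters at nominal visit times, and the two coefficients designated as the effects of interest cannot be estimated. Any pre/post coefficient left after dropping a term differs from the T2-to-T3 change by a multiple of the T3-to-T4 change: 13/12 if the interaction goes, 16/12 if time goes. This rests on nominal weeks 3, 16 and 28; using actual visit dates does not help in practice.

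Exclusion of every participant is conditional on reading the data rule outcome by outcome. The scope is one secondary outcome in a single-arm pilot. The opportunities-to-move outcome, with all four waves, does not share this rank problem, and neither the future sample-size calculation nor any progression criterion depends on the coefficient at fault. It should still be corrected, because the plan as written cannot be followed for this score.

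**What to change.** In Data analysis, exempt the risk score and its blood components from the segmented model and from the T1 requirement. Analyse T2, T3 and T4 in a mixed model with wave as a factor and random effects for person and office. Report T3 − T2 and T4 − T2 with 95% CIs, and state that these changes are not adjusted for any prior trend. This brings the analysis section into line with the secondary outcomes section.

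State also whether the T1-T2-T3 rule works per participant or per outcome, and to which analyses it applies.

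As a useful clarification rather than the correction of a demonstrated error, name the T2 mean and SD of the log10 values as the reference for standardising all three waves.

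The cost is a few sentences in the analysis and scoring sections, with no new data and no change to visits. Measuring the bloods at T1 as well would make all four coefficients estimable, but it adds a blood collection that the recommended fix does not need.
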